c.1236G > A/ HapB3 (rs56038477)	4.3–4.7%	Partial function	1.72 (1.22–2.42)

^a^European Caucasian data

Screening for *DPYD* variants prior to FP exposure allows an opportunity to dose-adjust FP chemotherapy regimens to make treatment more tolerable. Collaborative guidelines are in place to guide dosing decisions centred around which *DPYD* variants patients carry and tolerance of treatment, including those published by EviQ that guide dosing decisions in Australia [23]. While these guidelines do not mandate upfront *DPYD* screening, they support clinician-patient discussion and shared decision making.

A similar gene-drug relationship exists for uridine-diphosphate-glucuronosyltransferase family 1 (*UGT1A1*) gene and irinotecan chemotherapy. Irinotecan is typically prescribed in the management of pancreaticobiliary, other upper gastrointestinal, colorectal, sarcoma and lung cancers. Each year, approximately 2000 Australian cancer patients are prescribed irinotecan. Up to 40% of patients administered standard doses of irinotecan will develop grade 3–4 toxicities including diarrhoea and neutropenia [24]. Approximately 9% of European-Caucasians carry a *UGT1A1* variant; however, there is substantial ethnic variability throughout Asia (up to 41% variant carriers) [24]. There are 3 commonly significant variants; *UGT1A1**6, *28 and *37, with *28 associated with the most significant functional deficit. Current guidelines recommend carriers homozygous for *UGT1A1* *28 and certain compound heterozygotes start with 70% of the normal irinotecan dose, but availability of supporting data outside of Europe is limited [24].

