## Methods/design

This is a single arm, non-randomised, multicentre prospective study. In recognition of the strong international data that show benefit for PGx-guided dosing, it is considered unethical for us to conduct a randomised controlled trial to directly compare the implementation and non- implementation of PGx-guided dosing. It is a collaborative, investigator-led initiative supported by a trial committee comprising researchers from most states in Australia.

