### Clinical assessment, data collection and storage

The clinical assessment schedule is summarised below (Table 3), where implementation is included in the assessment table and is discussed separately below.

**Table 3 Tab3:** GeneScreen 5-FU assessment schedule

Assessment Time-point	Data points collected	Comments
*Baseline*	Patient and cancer demographics FP chemotherapy data *DPYD* genotype status	FP containing regimens Chemotherapy indication
*Post-first FP dose*	Patient metrics FP dose and adjustments FP related toxicities Hospitalisations, ICU admissions, treatment-related death	G3-4 toxicities Time in hospital Time in ICU G5 toxicity-related deaths Dose reduction data
*Subsequent FP administration* *(capped at 60 days post-first dose)*	Patient metrics FP dose and adjustments FP related toxicities Hospitalisations, ICU admissions, treatment-related death	G3-4 toxicities Time in in hospital Time in ICU G5 toxicity-related deaths Dose reduction data
*No fixed time point*	Patient and clinician semi-structured interviews	Exploration of patient/clinician experience of genotyping process Clinician satisfaction with education/support resources, facilitators/barriers to ongoing use
*Follow-up*	Cancer outcomes reports at 6-month intervals up to 5 years post-FP	Disease-free survival (DFS) Progression-free survival (PFS) Overall survival (OS) All cause mortality

Initial assessment will include patient demographics, tumour data and chemotherapy indication (curative/palliative). Chemotherapy regimens and FP dosing will also be collected. Clinical parameters including height and weight and haematological results prior to each cycle will be recorded. Dates of *DPYD* sample collection and results will be recorded, as well as the variant carrier status (including *UGT1A1* where applicable).

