#### Historical comparators

We felt it was unethical to have a control group of patients with *DPYD* variants who undergo standard FP dose administration due to the well described increased risk of toxicity within this population [9, 10]. Therefore, comparator populations for this project will include:Current standard of care, as assessed by a retrospective review of 500 consecutive cases in NSW [31].Contemporaneous cases without these *DPYD* variants treated with standard doses,*DPYD* variant carriers in this study that do not receive PGx-guided dose-adjustment, and.Patients treated in European cohorts whereby *DPYD* variant carriers were treated with a 25% or 50% FP dose reduction.

Background ≥ G3 toxicity in an ungenotyped population is approximately 17.4%, and in *DPYD* variant carriers without FP dose adjustment is reported to be 39–61% [8, 31]. Sub-analyses for each *DPYD* variant will be included.

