### Statistical considerations

#### Statistical hypotheses

We hypothesise that FP-induced severe toxicity (≥ G3) will decrease from 60% in the variant carriers receiving full dose chemotherapy to 35% in variant carriers receiving PGx-guided chemotherapy.

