#### Sample size determination

This project intends to capture and test most feasibly large cohort of patients based on average clinical volume and anticipated number of patients that are eligible for testing across all study sites. Approximately 17000 patients are treated with FP per annum, resulting in > 30,000 potentially eligible patients across just 2 years of recruitment. As such, 5000 subjects in this study would require a recruitment capacity of < 15%. Our participating sites provide care for > 30% of Australians with cancer.

Based on expected frequency of *DPYD* variant alleles (~ 4% as a conservative estimate), testing *N* = 5000 patients will result in ~ 200 patients with actionable genotypes. Toxicity in these patients will be compared to historical datasets (Table 4). Assuming toxicity decreases to 35% in those receiving PGx- guided dosing, *N* = 70/arm will provide 80% power to detect a significant improvement in FP-related toxicity at the 5% level.

**Table 4 Tab4:** Populations for analysis

**Analysis Population**	**Description**
Testing Set	All patients who are eligible for recruitment and undergo* DPYD* genotyping
*DPYD *Set	Patients in this study who are found to carry a *DPYD *variant. Comparator groups include: 1) retrospective review of FP toxicity in *n*=500 patients who were treated without genotyping 2) contemporaneous cases without *DPYD *variants treated with standard doses 3) contemporaneous cases of *DPYD *variant carriers who do not receive dose-adjustment, and 4) *DPYD* variant carriers in European cohorts who were treated with dose reduction

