### Statistical analyses

Descriptive statistics on continuous data will include means, medians, standard, deviations, and ranges, while categorical data will be summarized using frequency, counts and percentages. Graphical summaries of the data may also be presented.

The 95% confidence intervals for the proportion of tests returned within 7 days of intended chemotherapy dosing and the proportion of PGx guided dosing adjustments implemented will be estimated using the Clopper-Pearson method. PGx-guided dosing will be deemed feasible to implement if both 95% confidence intervals are completely above 80%.

The proportion of DPYD positive patients experiencing ≥ G3 toxicities in the current sample will be compared to the historical controls using a Fisher’s exact test. Logistic regression will also be used to compare the rate of ≥ G3 toxicities between the two groups. The intervention effect will therefore be summarised using the odds ratio and 95% CI from this model.

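### The effect of genotype-guided dosing is reported as a two-group odds ratio against non-randomised historical controls, with no adjustment named, so differences in source and case mix are credited to the dosing

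*Protocol article*

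**What the plan says.** The Methods/design section states: "This is a single arm, non-randomised, multicentre prospective study". Under Statistical hypotheses, severe toxicity "will decrease from 60% in the variant carriers receiving full dose chemotherapy to 35% in variant carriers receiving PGx-guided chemotherapy". Sample size determination expects that testing 5000 "patients will result in ~ 200 patients with actionable genotypes", and that 70 per arm "will provide 80% power to detect a significant improvement in FP-related toxicity at the 5% level".

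The Statistical analyses section then fixes the comparison. Carriers in the trial are set against historical controls by Fisher's exact test, and logistic regression compares the same rate between the two groups. It concludes: "The intervention effect will therefore be summarised using the odds ratio and 95% CI from this model". No covariate, matching, weighting or standardisation is mentioned.

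Three other places bear on this:

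- Clinical assessment, data collection and storage: "Initial assessment will include patient demographics, tumour data and chemotherapy indication (curative/palliative"). Regimen, FP dosing and variant status are also recorded.
- Historical comparators: four comparator populations are listed, and sub-analyses for each *DPYD* "variant will be included".
- Table 1 (Background): relative risks of toxicity at standard dose differ by variant. The lowest is for HapB3 (1.72, 95% CI 1.22–2.42) and the highest for c.1679T>G (4.40).

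**The concern.** Fisher's test is unadjusted by construction. A logistic model containing only a group indicator gives the same crude contrast on the odds scale. In a non-randomised comparison with historical data, that contrast mixes the effect of dosing with every other difference between the groups: which variants they carry, which regimens they received, treatment intent, and how toxicity was ascertained in each source. The plan nevertheless labels the result as the effect of the intervention. Its confidence interval would describe sampling error only, and a narrow interval around a confounded number could be taken as evidence for national roll-out.

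**Working it through.** **1. The plan's own figure.** Inputs: 60% and 35%, 80% power, 5% level (two-sidedness assumed, as it is not stated). The mean proportion is 0.475.

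n = [1.96·√(2·0.475·0.525) + 0.8416·√(0.60·0.40 + 0.35·0.65)]² / 0.25² = (1.384 + 0.575)² / 0.0625 = 61.4, so 62 per arm. With continuity correction, n = (61.4/4)·[1 + √(1 + 4/(61.4·0.25))]² = 69.2, so **70 per arm**, as stated. The planned odds ratio is (0.35/0.65)/(0.60/0.40) = 0.36.

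**2. Spread between reported rates with no intervention.** Historical comparators gives 39–61% for carriers without dose adjustment, a range of 22 points. Against 60%, a treated rate of 35% is a 25-point benefit (odds ratio 0.36). Against 39% it is 4 points, with odds ratio (0.35/0.65)/(0.39/0.61) = 0.84.

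**3. Full-dose carrier rate implied by Table 1.** Midpoint frequencies are 1.2, 0.15, 1.3 and 4.5 (total 7.15) for c.1905+1G>A, c.1679T>G, c.2846A>T and HapB3.

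Mean relative risk = (1.2·2.85 + 0.15·4.40 + 1.3·3.02 + 4.5·1.72)/7.15 = 15.746/7.15 = 2.20.

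The 17.4% background is for an ungenotyped population, so the non-carrier rate is 17.4% / [1 + p(2.20 − 1)], where p is carrier prevalence:

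| Carrier prevalence p | Non-carrier rate | Full-dose carrier rate (× 2.20) |
|---|---|---|
| 8% (Background) | 15.9% | 35.0% |
| 4% (sample size section) | 16.6% | 36.6% |

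Applying 2.20 directly to 17.4% gives 38.3%. The gap to 60% is therefore about 22–25 points before any dose change.

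Sensitivity: putting all four relative risks at their lower limits gives a mean of 10.788/7.15 = 1.51 and a carrier rate of 25–26%. Putting all at their upper limits gives 23.159/7.15 = 3.24 and 48–52%, still 8–12 points below 60%.

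**4. Variant mix alone.** The HapB3 share of carriers is 4.5/7.15 = 63%. The other three variants have a pooled relative risk of (1.2·2.85 + 0.15·4.40 + 1.3·3.02)/2.65 = 3.02. Two baselines are used: 17.4%, and 60%/2.20 = 27.2%, which makes carriers average 60%. Moving from no HapB3 to all HapB3 changes the rate by baseline × (3.02 − 1.72), which is 22.6 and 35.4 points respectively.

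| Difference in HapB3 share | Baseline 17.4% | Baseline 27.2% |
|---|---|---|
| 57% v 69% (extremes of Table 1 ranges: 4.3/7.5 and 4.7/6.8) | 2.7 points | 4.2 points |
| 30% v 63% | 7.5 points | 11.7 points |
| 0% v 63% | 14 points | 22 points |

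Half of the 25 points (12.5) needs a share difference of 12.5/22.6 = 55 or 12.5/35.4 = 35 percentage points.

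**5. Regimen.** The documents give no toxicity rate by regimen, so there is nothing to compute.

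**The case against.** The strongest reply is that the article never calls the logistic model unadjusted, and a covariate list is commonly left to a SAP or full protocol that is not shown. That is correct: the unadjusted contrast is the natural reading, not a stated fact. It does not remove the point. The article does fix the test, the model, the effect measure and the interval, describes the model only as a comparison of two groups, and gives the result a causal label.

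A second reply is that the plan already has safeguards: per-variant sub-analyses, contemporaneous non-carriers, and contemporaneous carriers whose dose was not adjusted. These help. But the sub-analyses do not alter the pooled odds ratio and do not address regimen, intent or age. The unadjusted carriers are not a random group. If the plan's own feasibility criterion is met (over 80% of adjustments implemented), they number fewer than 20% of about 200, that is, fewer than 40.

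A reader might also infer stronger claims that the documents do not support:

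- **Variant mix alone could produce most of the 25 points.** An all-c.1905+1G>A group against an all-HapB3 group would differ by 18–19 points, but no such group is described. Even an all-c.1905+1G>A group against the Table 1 mix differs by only (2.85 − 2.20) × 15.9–16.6% = 10.3–10.8 points.
- **Variant moves risk 1.7- to 4.4-fold in this comparison.** Those relative risks are used here as carrier against non-carrier. Between carriers, the ratios to HapB3 are 2.85/1.72 = 1.66 and 3.02/1.72 = 1.76, or 2.6 at most for the rarest variant.
- **Regimen alone could produce the benefit.** No figure supports this, and the composition of the historical cohorts is not reported.

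**Conclusion.** The concern holds in this form: the effect that the plan will report is a two-group odds ratio against non-randomised historical controls, with no adjustment or standardisation named, so it cannot separate dosing from source and case mix.

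The larger risk is the choice of source. Reported full-dose rates span 22 points, and Table 1 with the 17.4% background implies about 35–37%. A crude contrast with a 60% source could therefore show nearly the full hypothesised benefit with no dose effect. That is a difference between sources, not a variant-mix effect. Variant mix plausibly adds about 3–12 points. Regimen is unquantified.

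These sizes assume that the Table 1 relative risks apply to the 17.4% background (or to 27.2% in the second variant-mix scenario), that carrier shares are proportional to the listed allele frequencies, and, for the central figures, that the relative risks are taken at their point estimates. The article does not say what drives the 39–61% range. Whatever drives it, the crude odds ratio inherits it.

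**What to change.** In Statistical analyses, make the reported effect a variant-standardised or covariate-adjusted estimate. Suggested content:

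- **Main estimate.** A logistic model with group, *DPYD* variant, FP agent and combination, curative or palliative intent, age and sex, standardised to the trial's carriers. Report a risk difference and an odds ratio, each with a 95% CI. At Table 1 frequencies c.1679T>G is 0.15/7.15 = 2.1% of carriers, about 4 of 200, so it will need to be grouped, for example with the other no-function variant.
- **Support.** Keep Fisher's test and the crude odds ratio, labelled as unadjusted.
- **Comparators with published rates only.** Standardise those rates by variant to the trial's mix.
- **Comparators with wild-type patients.** Set the carrier-versus-wild-type contrast in the trial beside the same contrast in that source, to reduce era and ascertainment differences. The in-trial wild-type comparator is already planned; the matching contrast in the source is the addition.

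The cost on the trial side is wording, since demographics, indication, regimen, FP dosing and variant status are already recorded. Full adjustment is possible only for comparators with patient-level genotype and regimen data. The 500-case review was treated without genotyping, so variant adjustment there depends on genotype being available. The interval may be somewhat wider than the crude one.

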### Health economic analysis

A modelled cost-effectiveness analysis will estimate the incremental cost per QALY gained of *DPYD* screening. Prevalence, intervention costs and toxicity-related hospital costs (associated with inpatient separations, emergency department presentations and outpatient care) incurred during the study period will be used to populate a decision analytic model with a one-year time horizon. Health outcomes and hospital costs for a comparator group (i.e. no genotyping) will be estimated using published literature, analysis of a linked dataset (from historical cohorts) and prospectively in GeneScreen 5-FU participants that have a known *DPYD* genotype but did not have dose-adjustment. One-way sensitivity analyses will be conducted for key model parameters including *DPYD* screening costs, prevalence of *DPYD* genotypes and health outcomes. Probabilistic sensitivity analyses will be conducted to evaluate the impact of parameter uncertainty on model outcomes and will be presented on a Cost-Effectiveness Acceptability Curve for a range of cost-effectiveness thresholds. A budget impact analysis will be developed to inform on the affordability of national uptake of *DPYD* testing to support implementation.

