## Background

Fluoropyrimidines (FP) are commonly prescribed and variably toxic chemotherapies. Over 16,000 adult Australians receive this chemotherapy per year for the treatment of colorectal, upper gastrointestinal, breast and head and neck cancers [1]. Globally, more than 3.5million patients receive FP chemotherapies [2]. FP is delivered either as intravenous (5-fluoruracil; 5-FU) or oral (capecitabine) preparations.

Between 10–40% of patients who receive FP therapy develop severe and life-threatening (National Cancer Institute Common Terminology Criteria for Adverse Events, CTCAE grade 3 and 4) toxicities, and up to 1% die as a result of toxicity (CTCAE grade 5) [3–5]. Typical toxicities include diarrhoea, mucositis, haematological toxicities (predominantly neutropenia and thrombocytopenia), cardiotoxicity and palmar-plantar erythrodysesthesia (hand-foot syndrome) [6]. Between 31–69% of severe toxicities can be explained by a deficiency in the dihydropyrimidine dehydrogenase (DPD) enzyme, encoded by the *DPYD* gene (Fig. 1) [7, 8]. DPD catabolises circulating 5-FU, allowing excretion of inactive metabolites [9]. People who are DPD deficient lack the capacity to adequately catabolise circulating 5-FU, creating a supratherapeutic build-up of active drug and excessive toxicities as a result. Testing for DPD functional activity is difficult and surrogate tests such as *DPYD* genotyping have been developed to overcome this, though no test has yet been devised that can accurately identify all patients at risk of severe FP toxicities [10].

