**Primary**	
Determine efficacy of upfront *DPYD* PGx-guided dose-adjustment on FP safety and toxicity of carriers of clinically significant *DPYD* variant alleles.	a) Frequency of serious FP-related toxicity in patients receiving FP chemotherapies: - Grade 3 and 4 toxicity (CTCAE v5), hospitalisations (including presentations not resulting in admission), ICU admissions and death (CTCAE v5, Grade 5). [5] - Case Report Forms (CRF) for toxicities Grade 3-5. b) Frequency of serious FP-related toxicity in *DPYD*variant carrier patientsreceiving FP chemotherapies: - Using same metrics as above.
Develop and implement strategies to address enablers and barriers identified in the feasibility study.	Using validated framework and including patient and clinician interviews [29, 30]
Determine cost-effectiveness of upfront* DPYD* genotyping and personalised dosing and estimate healthcare benefits of full implementation of *DPYD PGx*-guided dose-adjustment in an Australian population.	a) Health economic and cost-effectiveness analysis of upfront *DPYD* screening and PGx-guided dose-adjustments / individualisation. b) Apply health economic modelling to illustrate cost burden and cost-effectiveness of pre-emptive *DPYD* screening on health care services.

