Data from patients will be collected from clinical presentations within the first 60 days of their first FP dose to identify grade 3 and 4 toxicities requiring hospital presentation with or without admission, ICU admissions and deaths related to FP toxicities. Grading will be in accordance with the current CTCAEv5 [5]. For patients who carry *DPYD* variants and undergo dose-adjustments, FP dosing trends and adherence to/utility of the guidelines will be recorded. Patient follow-up data will be collected for 5 years to determine long-term cancer outcomes (DFS, PFS and OS). Data will be collected, de-identified and stored on a secure REDCap database. Patient samples will be de-identified and bio-banked.

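### The cost-per-QALY model is fixed at a one-year horizon, which truncates life-years from averted toxic deaths and ignores any later survival difference, although survival is collected for five years

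*Protocol article*

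**What the plan says.** The Health economic analysis section states: "A modelled cost-effectiveness analysis will estimate the incremental cost per QALY gained" of screening. The vehicle is a "decision analytic model with a one-year time horizon", populated with prevalence, intervention costs and hospital costs related to toxicity. No rationale for the horizon, no extrapolation and no longer scenario is given. On uncertainty it says: "One-way sensitivity analyses will be conducted for key model parameters including" screening costs, genotype prevalence and health outcomes, and it adds probabilistic analyses for parameter uncertainty.

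Elsewhere in the article:
- Table 2 places the objective beginning "Determine cost-effectiveness of upfront" genotyping under Primary, although the text before the table counts cost-effectiveness among the secondary endpoints. Grade 5 toxicity is part of the primary toxicity endpoint.
- The Background puts toxic death at up to 1% of treated patients.
- Study population admits both curative and palliative treatment.
- Table 2 makes cancer outcomes under dose-adjusted treatment a secondary objective, and Table 3 schedules "Cancer outcomes reports at 6-month intervals up to 5 years post-FP".

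**The concern.** A QALY model has to value death. Toxic deaths that screening prevents would fall early, while the life they preserve runs on for as long as the patient would otherwise have lived. With a one-year horizon that benefit is cut at month 12 whatever the prognosis, and the cut is deepest for curative-intent patients.

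The same horizon removes any difference in cancer survival that emerges later. The trial treats this as an open question: it is a secondary objective, and the Discussion expects better cancer outcomes because more patients complete treatment. Whichever way survival moves, a difference after month 12 counts as zero.

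The resulting ratio is meant to support national roll-out, so a reader of the result would want to know how far it depends on the horizon.

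**Working it through.** The article reports no QALY or life-year figure, so there is no planned number to reproduce. The horizon is a design choice, and the check is what that choice does to life-years.

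**Inputs from the article:** horizon 1 year; survival follow-up 5 years; toxic deaths captured within 60 days of the first dose.

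**Assumptions, not in the article:** exponential survival with median m of 1, 2, 5 or 10 years; toxic death at day 30, so t0 = 30/365.25 = 0.082 years; no discounting; 60 years taken as lifetime.

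**Life-years credited per averted toxic death up to horizon T:**

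LY(T) = [1 − exp(−λ(T − t0))]/λ, with λ = ln 2/m.

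Example, m = 1: λ = 0.693.
- T = 1: [1 − exp(−0.693 × 0.918)]/0.693 = 0.471/0.693 = 0.68.
- T = 5: [1 − exp(−0.693 × 4.918)]/0.693 = 0.967/0.693 = 1.39.

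| Median survival | 1 year | 5 years | Lifetime | 1-year share of 5-year | 1-year share of lifetime |
|---|---|---|---|---|---|
| 1 y | 0.68 | 1.39 | 1.44 | 49% | 47% |
| 2 y | 0.79 | 2.36 | 2.89 | 33% | 27% |
| 5 y | 0.86 | 3.57 | 7.21 | 24% | 12% |
| 10 y | 0.89 | 4.17 | 14.2 | 21% | 6% |

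Discounting at an assumed 5% gives 0.66 to 0.87 at one year, 1.31 to 3.71 at five years and 1.34 to 8.34 over a lifetime. The shares hardly change at five years (23% to 51%) and are 10% to 49% of lifetime.

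The number of deaths averted cancels from these shares, and so does a constant utility weight. They therefore do not depend on an assumed mortality in carriers.

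**A hypothetical survival difference.** Suppose a constant hazard ratio h from the start. Mean life-years to T are [1 − exp(−hλT)]/(hλ), and the loss is the value at h = 1 minus the value at h.
- m = 1, h = 1.3: loss 0.062 at one year and 0.300 at five years, a share of 21%.
- m = 10, h = 1.1: loss 0.003 and 0.068, a share of about 5%.

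Across m = 1 to 10 and h = 1.1 to 1.3, one year captures about 5% to 21% of the five-year loss. A survival gain would be truncated in the same way. A difference that begins only after month 12 is captured at 0%.

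**Direction.** Cutting life-years from averted deaths understates the benefit of screening. Leaving out a late survival loss would overstate it, and leaving out a late gain would understate it. The article fixes neither the size nor the sign of a late difference, so the net bias has no known sign.

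**The case against.** The best defence is that the model is built around acute toxicity, whose clinical capture is "capped at 60 days post-first dose". A short horizon is a simple and recognisable choice for such events, and truncating averted deaths works against screening. This stands for acute hospital costs. It does not justify the horizon for QALYs that include death, and the conservative direction covers only one of the two omissions.

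Four stronger readings are tempting, and the document does not support them.
- *That the model leaves out the largest benefit and the largest harm.* The article ranks neither. Toxic death is put at up to 1% of all treated patients, while severe toxicity in carriers is hypothesised to fall from 60% to 35%. Nothing in the article shows that adjusted dosing worsens survival, and the dosing plan allows up-titration after the first administration.
- *That a horizon analysis has been ruled out.* The sensitivity list is open-ended, and a full economic plan may add scenarios. What holds is narrower: the named parameters, varied within a one-year structure, cannot recover what lies beyond it.
- *That one year clashes with the 60-day window, so later toxicity costs must be assumed.* The 60-day cap applies to clinical toxicity capture. The economic section draws on costs incurred during the study period and does not apply that cap to them.
- *That the understatement is fivefold.* Five years against one is a ceiling that needs every averted death to gain five full years. The illustration gives about 2-fold (1.39/0.68) to 4.7-fold (4.17/0.89).

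One further objection shapes the fix. The study is single-arm, with about 200 carriers expected. The 500 historical cases were treated without genotyping and at 4% would include about 20 carriers (500 × 0.04). If the 80% implementation criterion is met, fewer than 40 concurrent carriers (200 × 0.20) would be unadjusted. The collected survival data therefore cannot give a clean incremental effect of dose adjustment.

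**Conclusion.** The point holds as a worthwhile, inexpensive improvement rather than an error that invalidates the analysis. The one-year horizon is stated without justification for an outcome that counts deaths, in a cohort that includes curative-intent patients. It truncates life-years from averted toxic deaths and sets any survival difference after month 12 to zero. Under the stated exponential assumptions, one year credits about 0.7 to 0.9 life-years per averted death against about 1.4 to 4.2 over the five years of planned follow-up. These are life-years, not QALYs, and they rest on assumed prognosis. The effect on cost per QALY is of unknown sign.

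**What to change.** Keep one year as the base case and state why. Beside it:
- Pre-specify a discounted five-year scenario and a lifetime scenario by extrapolation.
- Use the collected OS to describe how long participants live.
- Enter any effect of dose adjustment on survival as a parameter varied over a range that includes no effect, not as an estimate taken directly from this single-arm cohort.
- Add time horizon to the listed sensitivity analyses.

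This needs modelling only, with no new patients, visits or data items. The downside is that the longer scenario depends on extrapolation when the first results are reported, or has to be updated once follow-up matures.
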